**Fig. 3 Fig3:**
[figure not shown]
Anti- hypertensive regimen. Note: Medications are prescribed in the absence of any contraindications

The study will be conducted by a multi-disciplinary team of trained emergency clinical medicine and public health researchers in two urban health environments: an emergency department and an academic clinical research center. Under the supervision of a research physician, patient screening, enrollment, baseline assessment and the first education intervention will be conducted by research assistants at the emergency department. The research physician will then review medication orders and provides instructions for the participant at enrollment. All subsequent study visits will occur at the clinical research center (CRC) about one mile away. At the beginning of each visit, the research physician and his clinical research team will review medication side effects, conduct pill counts and provide medication refills at seven, thirty and ninety day visits, with a three month prescription at the 180 day follow-up. Graduate level public health students will conduct post and follow-up interviews and facilitate patient education for the intervention group.

To promote retention, reminder calls and/or email will be done several days in advance and contact information will be updated at each visit. Both groups will be encouraged to monitor their blood pressure on their own and follow-up with a primary care physician. Participants missing visits and not responding to up to three reminder communication will be considered lost to follow-up. Participants will be withdrawn from the study for reasons such as withdrawing consent or moving too far away.

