**Methods/Design:**

Achieving Blood Pressure Control Through Enhanced Discharge (AchieveBP) is a behavioral RCT patient education intervention for patients with a history of hypertension who have uncontrolled BP at ED discharge. The project will recruit up to 200 eligible participants at the ED, primarily African-American, who will be asked to return to a nearby clinical research center for seven, thirty and ninety day visits, with a 180 day follow-up. Consenting participants will be randomized to either an attention-control or kiosk-based interactive patient education intervention. To control for potential medication effects, all participants will be prescribed similar, evidenced-based anti-hypertensive regimens and have their prescription filled onsite at the ED and during visits to the clinic. The primary target endpoint will be success in achieving BP control assessed at 180 days follow-up post-ED discharge. The secondary aim will be to assess the relationship between patient activation and self-care management.

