### Consent and Randomization

Figure 2 shows the flow of the participants through the study. Pre-screening will be conducted by trained research assistants. Prior to consent, patients will be informed the enrollment process could take about an hour to complete. Once identified, research staff will meet with the potential participants to describe the study, answer questions, and obtain consent. After signed consent, project staff will use the CAGE questionnaire to screen for substance abuse disorders. Those who score two or more will be considered ineligible and dropped from the study. Up to 200 adults will be enrolled (i.e., 100 per study arm with oversampling by 50 % to account for attrition). A second BP reading will be obtained prior to randomization to verify that the high BP readings taken during initial screening remain at the eligibility level.

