### Statistical analysis

The OnCore Clinical Trial Data Management System, which is internet accessible and HIPAA compliant, will be used for protocol management & data entry. Primary analyses will be conducted using IBM SPSS (v. 20). Initial analyses will consist of descriptive statistics including univariate and bivariate frequency distributions. Differences in baseline socio-demographic and medical variables between the two groups will be used as covariates if appropriate statistical assumptions are met. Tests of the hypotheses will use the intent to treat analysis and all available outcome data.

To assess if the intervention improves blood pressure control over standard discharge practices, differences between groups will be assessed using blood pressure as a continuous variable (i.e., changes in systolic/diastolic readings) and as a dichotomous variable (i.e., number of patients with controlled blood pressure.

A generalized linear mixed model analysis will be used to test differences between groups over time, using continuous blood pressure measures. Both groups are expected to show decreases in blood pressure over time but with greater decreases for the intervention group. Thus, for the continuous blood pressure measures, the major effect of interest will be the linear group x time interaction. We assume that decreases in blood pressure over the time periods will be roughly linear, although a quadratic time effect may also occur. Based on a standard deviation of 12 mmHg for systolic blood pressure, a clinically relevant decrease of 6 mmHg systolic blood pressure (i.e., d = .5), and a one-sided alpha of .05, the study will have adequate power (.80) with 50 subjects in each group. This is a somewhat conservative estimate which does not take into account repeated measures, blocking, or possible covariate adjustments, all of which would tend to increase power.

Group differences in decreased percentages of those with uncontrolled blood pressure will be compared at each time point. Percentages will be compared using the arc sine transformation. For power assessment, we assume a medium effect size of h = .5 [45], where h is the difference between arc sine values for the population proportions of the two groups. Illustrative pairs of proportions for h = .5 are 60–35, 65–40, 69–45, and 79–50. For these effect sizes, *n* = 50, and a one-sided alpha of .05, power would be .80. General linear models will be used to test the full range of assessment periods.

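### The loss-to-follow-up and relocation rules are not tied to day 180, so they can end outcome assessment before the primary endpoint and risk bias in the BP-control comparison

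*Protocol article*

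**What the plan says.** The Abstract (Methods/Design) fixes the endpoint: "The primary target endpoint will be success in achieving BP control assessed at 180 days follow-up post-ED discharge". Study outcomes repeats the 180-day control proportion and adds the difference in actual BP readings.

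Two retention rules stand under Study procedures. The first is "Participants missing visits and not responding to up to three reminder communication will be considered lost to follow-up". The second is "Participants will be withdrawn from the study for reasons such as withdrawing consent or moving too far away". Neither names a visit. The same section places every post-ED measurement at one site: "All subsequent study visits will occur at the clinical research center (CRC) about one mile away".

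Statistical analysis then states: "Tests of the hypotheses will use the intent to treat analysis and all available outcome data". Consent and Randomization sets enrolment at "100 per study arm with oversampling by 50 % to account for attrition".

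**The concern.** Follow-up visits fall at days 7, 30, 90 and 180. Because the rules name no visit, a participant who misses day 7 or day 30 and does not answer the reminders already meets the definition of lost. A participant who moves is withdrawn from the study as a whole, by the study's decision, in the same sentence as withdrawn consent. The article does not distinguish ending the education from ending outcome assessment, and it describes no attempt to obtain the 180-day BP from these people.

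An outcome that was never sought cannot be restored by an analysis of all available data. Loss is plausibly related to outcome, because study refills and medication titration take place at the same visits, so people who miss visits also miss those contacts. It may differ by arm, because three of the four kiosk sessions take place at those visits and only the intervention arm has them. If both happen, the observed day-180 control proportions no longer compare the groups as randomised, and enrolling more participants does not correct that.

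**Working it through.** **1. The plan's own power figure.** Inputs from Statistical analysis: SD 12 mmHg, difference 6 mmHg (d = 6/12 = 0.5), one-sided alpha .05, 50 per arm.

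- Normal approximation: power = Φ(0.5 × √(50/2) − 1.645) = Φ(2.5 − 1.645) = .804. The noncentral t gives .799.
- The arcsine comparison with h = .5 has the same form and gives .804.

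The stated .80 is reproduced.

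**2. The attrition allowance.** 50/(1 − 0.5) = 100 per arm reproduces the enrolment figure; 50 × 1.5 would give only 75. The design therefore tolerates loss of half of each arm. This is an allowance, not a forecast of loss.

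**3. Power against loss.** With 100 enrolled per arm, n = 100 × (1 − loss), same inputs, one-sided:

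| Loss at day 180 | n per arm | Power |
|---|---|---|
| 0% | 100 | .971 |
| 20% | 80 | .935 |
| 40% | 60 | .863 |
| 50% | 50 | .804 |
| 60% | 40 | .723 |

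Power falls below .80 only beyond about 50% loss.

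**4. Bias illustration.** The rates here are assumed; none is in the article. In both arms 60% are engaged with 60% control and 40% are disengaged with 30% control. True control is .6 × .6 + .4 × .3 = .48 in each arm, so the true difference is 0. Suppose all the engaged are seen at day 180 and a share L of the disengaged is lost. Then

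observed control = (.36 + .4 × (1 − L) × .30) / (.6 + .4 × (1 − L)).

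- L = 50%: (.36 + .06)/.80 = .525 (20% of the arm lost)
- L = 75%: (.36 + .03)/.70 = .557 (30% of the arm lost)
- L = 100%: .36/.60 = .600 (40% of the arm lost)

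Spurious differences between arms:

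- 50% v 50%: 0 points
- 75% v 50%: .557 − .525 = about 3 points
- 100% v 50%: .600 − .525 = 7.5 points

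The arm that loses more of its disengaged participants looks better, so the sign depends on which arm that is. For scale, the plan's illustrative pair 60–35 is a 25-point difference, and 7.5/25 = 30% of it.

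**5. The two together.** The largest of these cases loses 40% and 20% of the arms, inside the allowance in step 2. With 60 and 80 analysed, the effective n per arm is 2 × 60 × 80/140 = 68.6, and power = Φ(0.5 × √(68.6/2) − 1.645) = Φ(1.28) = about .90. A trial can keep its planned power and still carry this bias.

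**The case against.** The strongest reply is that the first rule only classifies. It does not say that one missed visit ends follow-up, and it does not forbid a later contact or turn away someone who comes back. The absence of a stated route back is silence in a condensed article whose flow chart is not reproduced in the text at hand. This stands in part: a reader might infer that participants are barred from the day-180 visit, and the text does not say so. What remains is that the article states the classification without tying it to the endpoint visit, and that relocation leads to withdrawal from the study in plain terms.

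Second, a reader might infer that those lost drop out of the analysis, or that the plan contradicts its intent-to-treat claim. Neither follows. Nothing says that earlier data are discarded, and readings before loss still enter the mixed model for continuous BP. How missing values are handled may be set out in an analysis plan not shown. The concern therefore bears mainly on the day-180 control proportion.

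Third, the article does address retention: advance reminders, contact details updated at each visit, and logistic regressions exploring differences in study completion. These are useful, but the first two do not cover a participant already classed as lost, and the last describes loss without preventing it.

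Fourth, a reader might infer that half the outcomes are expected to be missing, or that the rules leave the trial underpowered. The 50% is an allowance, and .80 is the power after all of it is used.

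Finally, some people who ignore every contact cannot be reached under any rule, and a phone call cannot supply the BpTRU reading for someone who has moved. Only part of the loss is avoidable, and the article gives no basis for saying how much.

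**Conclusion.** The concern holds in limited form. As written, both rules can end outcome assessment before the 180-day endpoint, and the article states no attempt to obtain that endpoint afterwards. This weakens the intent-to-treat comparison of BP control at day 180 but does not openly contradict it. The harm to guard against is bias; power is protected up to about 50% loss on the plan's one-sided test.

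The size of the bias is unknown. The range of 0 to 7.5 points rests wholly on assumed control rates, an assumed disengaged share and assumed loss patterns. It requires loss that is related to outcome and also unequal between arms; with equal loss in this illustration the spurious difference is zero. It also does not separate loss caused by the rules from loss that would happen anyway. The documents do not show that differential loss will occur. The change is worth making because it is cheap and protects the primary comparison.

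**What to change.** Amend Study procedures as follows:

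- Separate stopping the educational intervention from stopping outcome assessment.
- Invite every randomised participant who has not withdrawn consent to the 180-day BP assessment, whatever visits were missed.
- For the primary endpoint, class a participant as lost to follow-up only after the day-180 contact attempts have failed.
- Remove relocation as a study-initiated withdrawal. Still invite movers to the day-180 visit and keep their ED returns, which the article already takes from medical records. Accept that BP will be missing if they cannot attend.
- Record the reasons for loss by arm.

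The cost is a few extra calls per participant who misses visits and a short amendment. Some non-responders will remain unreachable, so missing day-180 outcomes will be reduced, not removed.

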### Intervention

An evidence-based patient education hypertension curriculum, developed by American TeleCare, Inc., will be provided through a portable touch screen kiosk (Aviva® 200: InLife™ XP Patient Monitor/LifeView™ Video Patient Station). The series of four modules are designed to provide patient education about BP control and to help build lifestyle decision-making skills. The hypertension curriculum, which was used in the investigator feasibility study, was developed in 2006 and revised in 2011. For the present study, the first kiosk session will be completed in the ED. A second kiosk located in the research facility will be used for three subsequent sessions to be completed at the 7, 30, and 90 day visits.

Research staff will show participants how to use the kiosk and will remain close by to answer questions that may arise. If desired, the kiosk can be set to read the material aloud and participants can control the pacing of the material by touching the screen when they are ready for the next item. Once the session is completed the kiosk will send the encrypted information to a secure place on the ATI server for storage and review by the research team.

The beginning of each session walks the participant through the steps of taking his/her own BP using the attached monitor. The kiosk automatically records the reading and asks a series of questions about factors that could influence the readings (e.g., resting period, time since last consumed beverage and type of beverage). The measurement is followed by a series of hypertension health facts and associated true/false questions. If a participant answers a quiz item incorrectly, the associated health fact is repeated to reveal the correct answer. Flesch-Kincaid reading level [39] for the sessions is grade level 5.9. The first session, which will be provided at the baseline emergency department discharge visit is “What is Hypertension?” containing eight health facts and two quiz items. Subsequent topics to be covered during the follow-up visits include hypertension risk factors, suggestions on how to modify risks under their control, and the complications of uncontrolled BP. Although the number of health facts and quiz items vary by module, the average session will take about fifteen minutes. The health education modules will include definitions of blood pressure and hypertension, hypertension risk factors, the effects of drug and alcohol use on blood pressure, and the complications of poor blood pressure control. Sample health fact and quiz items are shown below in Table 2.

**Table 2 Tab2:** *Achieve*BP patient education kiosk modules

Session	Module/Topic	Content example
1. Baseline	Blood Pressure and Hypertension Definitions	"Hypertension" is the medical term for high blood pressure. A person with high blood pressure is sometimes described as "hypertensive."
	Essential vs. Secondary Hypertension	Normal blood pressure is a systolic pressure of 120 or less. "Systolic" is the top number in a blood pressure reading.
	Systolic and Diastolic Normal Readings	
2. Seven Day	Hypertension Risk Factors	High blood pressure has many risk factors. Some you can't control. Family history - High blood pressure tends to run in families.
		Other risk factors for high blood pressure are within your control: Too much sodium (salt) in your diet which can cause your body to retain fluid, which increases blood pressure.
3. Thirty Day	Tobacco and Alcohol Use	If you drink more than moderate amounts of it, alcohol can actually raise blood pressure by several points. It can also reduce the effectiveness of high blood pressure medications.
	Caffeine Use	
		Cut back on caffeine. The role caffeine plays in blood pressure is still debatable. Drinking caffeinated beverages can temporarily cause a spike in your blood pressure, but it's unclear whether the effect is temporary or long lasting.
4. Ninety Day	BP Complications	Hypertension is frequently called the "silent killer" because it rarely causes symptoms. This is dangerous because untreated hypertension can lead to strokes, heart attacks, kidney disease, and vision loss.
	Complications of Uncontrolled Blood Pressure	
		Very high blood pressure is dangerous. You should call your Healthcare Provider anytime day or night, if your resting systolic blood pressure is over 180 or your resting diastolic blood pressure is over 110.

### Study outcomes

#### Primary outcome measure

The primary health outcome measure is short-term patient BP control. Blood pressure will be assessed using the BpTRU device (Smiths Medical PM, Inc; Waukesha, WI) which provides up to six automated measurements with initiation of the process by the patient rather than a health care provider. Blood pressure will be taken using this device at all assessment periods. Both the difference in the actual BP readings and the proportion of persons in each group achieving BP control at 180 days will be used to assess study outcomes. BP control is defined as at or below 140/90 for non-diabetics and at or below 130/80 for diabetics.

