## Methods

### Study design and aims

Achieving Blood Pressure Control Through Enhanced Discharge (AchieveBP) is a behavioral patient education intervention. It is a longitudinal, randomized controlled study in which ED patients with uncontrolled hypertension receive either an educationally enhanced or a standard discharge procedure. Study outcomes are assessed at baseline, 30, 90, and 180 days post ED discharge.

The design and conduct of the study adheres to the Consolidated Standards of Reporting (CONSORT) guidelines [37]. The study was approved by the Wayne State University Medical Institutional Review Board (M1, IRB#050213M1F) on 23 July 2013, and is registered with ClinicalTrials.gov (#NCT02069015). The study is administered through the Department of Family Medicine & Public Health Sciences in partnership with the Department of Emergency Medicine at the Wayne State University School of Medicine. Results of this study will be disseminated via scientific forums, including peer-reviewed publication and presentations at national and international conferences.

The primary aim of the study is to determine if integrating kiosk-based patient education via health information technology into the ED discharge process, coupled with additional educational sessions outside the ED will improve BP control compared to the usual discharge process. The secondary aim is to explore the relationship between patient activation, self-management behaviors (e.g., BP medication adherence), and health care utilization (i.e., return hospital emergency department visits). Cost effectiveness of the intervention will be assessed as well.

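### The protocol does not settle which blood pressure result decides the primary aim: 180-day control, the continuous readings, or both

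*Protocol article*

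**What the plan says.** Three places in the protocol article bear on what decides the primary aim.

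- **Abstract, Methods/Design.** One endpoint, one time: "The primary target endpoint will be success in achieving BP control assessed at 180 days follow-up post-ED discharge".
- **Study outcomes, Primary outcome measure.** The section opens by naming short-term BP control as the primary measure, then says that study outcomes will be assessed by "Both the difference in the actual BP readings and the proportion of persons in each group achieving BP control at 180 days".
- **Statistical analysis.** The intervention question is to be answered with "blood pressure as a continuous variable (i.e., changes in systolic/diastolic readings) and as a dichotomous variable". On the continuous side, "for the continuous blood pressure measures, the major effect of interest will be the linear group x time interaction". On the binary side, "Group differences in decreased percentages of those with uncontrolled blood pressure will be compared at each time point". Study design and aims gives the schedule: "Study outcomes are assessed at baseline, 30, 90, and 180 days post ED discharge", so there are three post-baseline comparisons.

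Power is given twice. For systolic BP (SD 12 mmHg, difference 6 mmHg, d = .5) the text reads "a one-sided alpha of .05, the study will have adequate power (.80) with 50 subjects in each group". For the control proportion (h = .5) it gives the same alpha, the same 50 per group and the same .80. The paragraph after these analyses introduces the patient-activation hypotheses as additional to the primary outcome, which leaves all the BP analyses on the primary side.

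**The concern.** The three places do not describe the same primary result. The Abstract has one binary endpoint at one time. The outcomes section puts a continuous measure beside it under the primary heading. The analysis section changes the continuous measure from a difference in readings to a slope over all visits, for two pressures, and widens the binary comparison from day 180 to every visit.

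These results can disagree. A difference in slope can appear without a difference in control at day 180, and a difference in mean pressure need not move enough patients across the threshold. The text does not say which result would then answer the primary aim, so the choice could be made after the data are seen. If any one of several one-sided .05 tests is enough, the chance of a false claim exceeds 5%.

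**Working it through.** **1. The plan's own power figures.** Inputs from Statistical analysis: 50 per group, one-sided alpha .05 (z = 1.645), d = 6/12 = .5, h = .5.

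- Systolic BP: Φ(d·√(n/2) − z) = Φ(.5·√25 − 1.645) = Φ(.855) = .804. The noncentral t calculation gives .799.
- Proportion: Φ(h·√(n/2) − z) = Φ(.855) = .804.

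Both stated values of .80 reproduce, and each uses the whole one-sided .05.

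**2. False-positive rate if any one test suffices, assuming independence.** The formula is 1 − .95^k.

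| Tests that could carry the claim | k | Rate |
|---|---|---|
| Systolic slope, 180-day control | 2 | 9.75% |
| plus diastolic slope | 3 | 14.3% |
| plus control at days 30 and 90 | 5 | 22.6% |

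**3. Allowing for correlation.** The tests share patients, so the true rates are lower. For equally correlated normal statistics, with correlation from .9 down to .3:

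- two tests: 6.8% to 9.3%
- three tests: 7.9% to 13.0%
- five tests: 9.5% to 19.4%

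**4. Patient-level simulation under no effect.** There were 50 per arm, visits at 0, 30, 90 and 180 days, and systolic SD 12 (from the protocol). Assumed, because the documents do not give them: diastolic SD 8, systolic–diastolic correlation .5 to .7, correlation between visits .3 to .7, mean pressures over time, and the non-diabetic threshold for everyone. Slopes were compared by a one-sided t-test and control by the arcsine test.

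- Systolic slope or 180-day control: about 8 to 9%.
- Adding the diastolic slope: about 11 to 12% (highest single run 12.7%).
- Adding control at days 30 and 90: about 19 to 20% (single runs 18.2% to 20.8%).

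**5. What each remedy does to power.**

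- One named primary test keeps the full one-sided .05, so power with 50 per arm stays at .80 (step 1).
- Two primary tests sharing the alpha have .025 each (z = 1.960): Φ(2.5 − 1.960) = .705 with 50 per arm, and .80 needs 2·(1.960 + .842)²/.5² ≈ 63 per arm.

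**The case against.** The strongest reply is that the document has one primary construct throughout. The Abstract, the primary aim and the opening of the Primary outcome measure section all say BP control. The sentence on using both measures does not itself call both primary, and the remark on the major effect is limited to the continuous measures, so it picks an effect within that model and sets up no rival endpoint. One-sided .05 appears only in the two power statements; no alpha is given for diastolic BP or for the earlier visits. Multiplicity rules are also often left to an analysis plan, which is not shown here.

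Much of this stands. The absence of a multiplicity procedure is not the fault. The fault is that the article fixes the primary result in ways that do not agree: continuous readings sit under the primary heading and have their own full-alpha power statement, while the Abstract has control alone. An analysis plan could follow either and claim to conform.

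Two stronger readings are tempting and are not supported.

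- A reader might infer that success may be claimed on any of five tests, with an error near 20%. The text says that proportions are compared at each visit. It does not say that an early difference meets the primary aim, and both the Abstract and the outcomes section place control at 180 days.
- A reader might infer that one-sided testing is itself part of the error and that power should be restated as about .70. One-sided .05 is stated openly and the .80 follows from it. Preferring a two-sided test is a separate matter, and it is not needed to resolve the inconsistency.

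**Conclusion.** The point holds as an inconsistency in the text about which BP result decides the primary aim. If the systolic slope and 180-day control, the two results for which power is claimed, are alternative routes to the primary claim, the false-positive rate is about 8 to 9% against a nominal 5%. It is about 11 to 12% if the diastolic slope is a third route. Both figures assume that each test is run at one-sided .05, which is the natural reading of the power statements but is not stated as a testing rule, and that any one result suffices, which the document neither says nor excludes. They also rest on the assumed diastolic SD, correlations and mean pressures. Very high correlation (.9) would lower them to 6.8% and 7.9%, still above 5%. The figure of 19 to 20% applies only if day-30 and day-90 control also counted as primary success, and should not be quoted as the error rate of this plan.

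**What to change.** In Primary outcome measure and in Statistical analysis, state that BP control at 180 days, as in the Abstract, is the single primary test. Make the continuous group by time analyses secondary, systolic first and then diastolic, in that fixed order. Label the day-30 and day-90 control comparisons descriptive.

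This is a change of wording. It adds no participants, and the stated power of .80 with 50 per arm (h = .5, one-sided .05) stands as the power of the primary test. The systolic calculation can stay, labelled as power for a secondary analysis. The downside is small: a positive continuous BP result alone could no longer be claimed as meeting the primary aim. If the investigators want the systolic slope to remain a second route to that claim, the alpha has to be shared, at the price shown in step 5 of the working.
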